## Introduction

1

There is still controversy and lack of consensus regarding not only surgical indications but also treatment of acute displaced clavicle shaft fractures and acute high-grade displaced acromioclavicular (AC) joint injuries (1–3). As surgical treatment has been increasingly used (1), higher complication and reoperation rates observed have led some to caution against overtreatment of displaced midshaft clavicular fractures (1, 4–6). After surgical treatment, reported reoperation rates in clavicular fractures range from 10%–84% (4–7) and up to 67% in AC joint dislocations (5). The need for plate removal is most often due to plate prominence and poor cosmesis due to the subcutaneous position of the clavicle and the bulky standard 3.5 mm implants. Galdi et al. examined whether using a lower profile 2.7 mm reconstruction plate would lead to better clinical outcomes and lower removal rates when compared with a 3.5 mm reconstruction plate in AO/OTA (Arbeitsgemeinschaft für Osteosynthesefragen/Orthopedic Trauma Association) type B clavicle fractures (8). The thinner 2.7 mm plates provided higher rates of cosmetic acceptability but did not demonstrate a statistically significant difference in reoperation rates for plate removal (8). Similarly, a recent retrospective comparative study also found that there was no statistically significant difference in rate of removal between 2.7 mm plates and 3.7 mm plates (9). Other studies have shown that clavicle fractures fixed with 3.5 mm reconstruction plates on the superior (subcutaneous) clavicle surface were more likely to exhibit plastic deformation, whereas constructs utilizing 2.7 mm reconstruction plates were more likely to fail by plate breakage (4).

The cost of clavicle fracture and AC dislocation treatment is high, ranging from a 2-year mean of US$27,635 [standard deviation (SD): US$68,173] to US$23,096 (SD: US$28,746), respectively (5), and up to GB£5000 for reoperations (7). Improving surgical methods and technologies could therefore reduce healthcare system costs through reduced unplanned reoperations and device removals. Additionally, predictable anatomic variance in clavicle morphology has been identified (10, 11), and understanding this variance could not only help improve the design and adaptation of clavicle implants, reducing the need for reoperations, but could also aid in implant selection (11).

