#### Data collection

2.3.4

Tables 2, 3 show data to be recorded for Clavicle Plates and Clavicle Hook Plates. Figure 1 presents the planned patient flow.

**Table 2 T2:** Study schedule for patients with clavicle plates (lateral, shaft, and medial).

Assessment parameters	Pre- intra- and postoperative visits*							
	Visit 1	Visit 2	Visit 3	Visit 4	Visit 5	Visit 6	Visit 7^#^	Visit 8^#^
	Screening/preoperative	Intraoperative (Day 0)	2 (±1) weeks	6 (±1) weeks	3 months (±2 weeks)	6 (±1) months	12 (±1) months	24 (±2) months
Patient information/consent^1^	X							
Eligibility^1^	X							
Patient characteristics	X							
Surgical details		X						
Adverse events		X	X	X	X	X	X	X
Device deficiencies		X	X	X	X	X	X	X
Bone healing				X	X	X	X	X
Surgeons’ evaluation		X						
QuickDASH	X^2^		X	X	X	X	X	X
Patient-reported outcomes^3^								
PROMIS Upper Extremity	X^2^		X	X	X	X	X	X
Local pain			X	X	X	X	X	X
Local discomfort			X	X	X	X	X	X
Plate prominence			X	X	X	X	X	X
Implant removal^π^			X	X	X	X	X	X
Images (x-ray/CT scan)^4^	X	X	X	X	X	X	X	X

CT, computed tomography.

* All postoperative follow-up visits with the defined time windows are calculated from the day of surgical treatment (i.e., Day 0).

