##### Patient-reported outcomes

2.3.7.6

PROs used in this study are the Patient-Reported Outcomes Measurement Information System (PROMIS®) (23), a set of person-centered measures that evaluate and monitor physical, mental, and social health in adults and children. The PROMIS® Physical Function Upper Extremity Short Form 7a v2.0 (2018) consists of seven questions to evaluate activities requiring use of the upper extremity (shoulder, arm and hand).

Additional PROs including local pain, local discomfort and plate prominence will be assessed using an NRS. The local pain NRS (24, 25), scale ranges from 0 (no pain) to 10 (worst imaginable pain), where pain NRS ≥5 (severe pain) will be considered as an AE. The NRS for local discomfort related to the plate ranges from 0 (no discomfort) to 10 (maximum degree of discomfort imaginable). Patients reporting discomfort NRS ≥1 will be asked if the discomfort produced by the plate requires medical or surgical treatment. If such treatment is required, it will be considered an AE. The plate prominence NRS ranges from 0 (no prominence) to 10 (maximum level of prominence). Patients reporting plate prominence NRS ≥1 will be asked if they require medical or surgical treatment to address the prominence. If treatment is required, it will be considered an AE.

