AEs will be reported both at patient level and AE level. The risk estimates will be presented along with the 95% Clopper-Pearson confidence interval. When calculating the AE rates, the denominator will be the full analysis population, irrespective of dropouts during FU. Sensitivity analyses will be conducted excluding patients who dropped out of the study and had not experienced an AE. For patients treated with Clavicle Plates, the risk of experiencing any ADE within 24 months after surgery will be reported. For the calculation of the ADE rate, only ADEs with onset before or within the upper visit window of the 24 months visit will be included. For patients treated with Clavicle Hook Plates, the risk of experiencing any ADE between surgical treatment and 12 months after removal of the Clavicle Hook Plate will be reported. Separate sub analyses on the risk of experiencing an ADE between surgery and Clavicle Hook Plate removal and within 12 months after the Clavicle Hook Plate removal will be performed. Separate ADE rates for the two FU periods including only ADEs with onset within the upper boundary of the visit window of the corresponding FU period will be calculated. For incidences of complaints related to plate prominence or discomfort and to local pain, incidence rates will be calculated, and summary statistics presented, including the number and percentage of patients with complaints related to plate prominence or discomfort (defined as NRS ≥1) and local pain (defined as NRS ≥3). For the reoperation rate due to ADE, fracture union rate, rate of stable AC joint healing at one-year post-removal, the full analysis population will be used as the denominator. Descriptive analyses on the rate of implants removed and the reasons for implant removal will be conducted. Simple summary statistics (i.e., numbers and percentages) will be produced for each bone healing category. QuickDASH, will be measured repeatedly during the FU period and analyzed using mixed effects models for repeated measures (MMRM). PROs also measured repeatedly during the FU period will likewise be analyzed using MMRM. For the surgeons' evaluation, simple summary statistics including numbers and percentages will be produced for each category.

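### Clavicle Plates: prominence and plate-related discomfort are scheduled and modelled to 24 months with no stop at implant removal, so plate-free scores can lower the late results

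*Protocol article*

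**What the plan says.** Section 2.3.7.6 makes the two scores patient-reported outcomes: "Additional PROs including local pain, local discomfort and plate prominence will be assessed using an NRS". It ties discomfort to the implant: "The NRS for local discomfort related to the plate ranges from 0 (no discomfort) to 10". Section 2.4.2 sets the analysis: "PROs also measured repeatedly during the FU period will likewise be analyzed using MMRM". No condition on the plate being in place is attached.

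**Clavicle Plates.** The Table 2 row reads "Plate prominence X X X X X X", which covers Visits 3 to 8 (2 weeks to 24 months). Local discomfort has the same six marks. Implant removal is marked as conditional at the same six visits; the two score rows carry no such mark. Section 2.3.4.5 counts all visits from implantation, and removal does not restart the clock.

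**Hook Plates.** Table 3 leaves prominence blank after removal, and the score at the removal visit refers to the status before that surgery. Local discomfort continues at Visits 7 to 9, all after removal. Those visits run on their own clock (Day 0′).

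**Link between removal and the outcome.** The Introduction states: "The need for plate removal is most often due to plate prominence and poor cosmesis". The Discussion names prominence as the leading cause of reoperation following plating of the clavicle shaft.

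**Reported separately.** Sections 2.3.7.7 and 2.4.2 provide for the rate of removal and its reasons, and 2.3.7.7 adds its timing.

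**The concern.** A prominence score describes a plate under the skin. Once the plate is out, the score no longer measures the device, and a value of 0 means only that there is nothing left to protrude. In the Clavicle Plate group these values would share visits with scores from plates still in place, because the clock does not restart.

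By the document's own account, patients who lose their plates are disproportionately those bothered by prominence. High scores would then be replaced by low ones, and the late curve would improve partly because plates were taken out. Low profile is the design rationale, and complaints about prominence or discomfort come first among the clinical performance outcomes in section 2.3.7.2. The late scores are therefore results that readers will look at closely.

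Table 3 shows that the distinction was recognised for prominence in Hook Plates; Table 2 does not carry it over. Section 2.4.2 likewise splits adverse device effects in Hook Plates at removal, but not the patient-reported scores.

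**Working it through.** **Inputs from the document.** The plan states no expected NRS, removal rate or hypothesis for these outcomes, so there is no planned figure of this kind to reproduce. The sample size does reproduce: 30/(1 − 0.20) = 37.5, rounded up to 38 per group, 2 × 38 = 76. The point does not depend on it; 30 per group serves only to turn percentages into patients.

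**Assumed inputs.** Share of plates removed by 24 months f = 10%, 20% or 30%; score before removal 6; score of retained plates 1.5; score after removal 0. The cited reoperation range of 10%–84% is background literature on clavicular fractures, not an expected removal rate for this device.

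**Formulas for the 24-month mean**
- As scheduled, plate-free zeros included: (1 − f) × 1.5 + f × 0
- Plates in situ only: 1.5
- Last in-situ score carried forward: (1 − f) × 1.5 + f × 6

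| f (of 30) | As scheduled | In situ | Carried forward |
|---|---|---|---|
| 10% (3) | 1.35 | 1.50 | 1.95 |
| 20% (6) | 1.20 | 1.50 | 2.40 |
| 30% (9) | 1.05 | 1.50 | 2.85 |

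The zeros lower the mean by f × 1.5 against plates in situ (0.15, 0.30, 0.45) and by f × 6 against the carried-forward value (0.6, 1.2, 1.8).

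**Removal unrelated to prominence.** If all plates score 2 and 20% are removed, the scheduled mean is 0.8 × 2 = 1.60 against 2.00 in situ. The direction does not need outcome-driven removal; the gap to the carried-forward value does grow with it.

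**Visit-wise percentages.** If 6 of 30 patients had NRS ≥1, had the plate removed for it and then score 0, the percentage at later visits loses up to 6/30 = 20 points.

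**Repeated-measures model.** A large simulation used six visits and removed mainly the plates scoring highest at 6 months, half of them before the 12-month and half before the 24-month visit. The 24-month mean with every plate left in place was about 3.05. At 10%, 20%, 30% and 50% removed, keeping the zeros gave 2.50, 2.06, 1.68 and 1.01. Setting post-removal scores to missing and estimating by likelihood gave 3.04 to 3.07. That recovery is built in: removal depended on the observed 6-month score plus independent noise, so the data were missing at random.

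**The case against.** **The zeros are assumed.** Nothing in the document says that a plate-free patient is asked about prominence or scored 0; the case report form may skip the item. This stands. The effect is conditional, and its true size is unknown.

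**The SAP is not shown and may deal with removal.** Populations, missing-data methods and covariates are deferred to it, and its silence here is no fault. But the collection schedule is fixed in this document, its two tables differ on the same item, and the missing-data text speaks only of withdrawal-type losses.

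**Removal is not always driven by the outcome.** The Discussion says that patients ask for removal for various reasons and that some plates come out routinely. This limits the size, not the direction.

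**A reader might infer that the whole device system is flattered.** The document does not support that. Hook-plate removal is a scheduled step with its own visits, not a device failure, and prominence stops there. Post-removal discomfort in that group can be legitimate data, since acromial effects of the hook could outlast it; the defect is only that the scale is defined as plate-related.

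**A reader might also infer that complaint rates in general improve, or that failures are hidden.** On a patient-level count, someone who complained before removal stays a case whatever is scored later. Removals and their reasons are reported, and prominence or discomfort needing treatment is an adverse event.

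**The gap of 1.2 points depends on the comparator.** It comes from carrying the last score forward. Against plates actually in situ the gap is 0.3.

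**Conclusion.** The point holds for Clavicle Plates, for both prominence and plate-related discomfort. Followed as written, the schedule and the MMRM sentence pool scores taken without a plate into late visit-wise means, visit-wise NRS ≥1 percentages and model estimates. For Hook Plates it is confined to plate-related discomfort at Visits 7 to 9. It does not reach hook-plate prominence or a patient-level count of those who ever complained.

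Under the assumed scores with 20% removed, the distortion at 24 months is 0.3 points against plates in situ and 1.2 against the carried-forward score. Both rest on post-removal values near 0 and on scores that the document does not give. The direction is secure if those values are near 0; the amount is not known. In a descriptive series this threatens the reading of the late prominence and discomfort results, not the study as a whole. It should be settled before the final analysis.

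**What to change.** 1. Add a footnote to Table 2: prominence and plate-related discomfort are scored only while the plate is in situ. This matches Table 3 for prominence.
2. Restrict the MMRM of these two scores to in-situ visits. State that likelihood estimation then treats scores after removal as missing at random, so the estimate describes plates as if they had stayed in. A flare between visits that leads to removal would not be captured.
3. Add a by-visit composite: a patient counts as a case if NRS is ≥1, or if the plate has already been removed for prominence, discomfort or pain. Say how removals for other reasons enter the denominator.
4. Keep collecting local discomfort, pain and function after removal in both groups, with discomfort then understood as local rather than plate-related. Report these apart from the in-situ results.

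The cost is a footnote, some SAP wording and slightly more analysis. The date of and reason for removal are already collected (section 2.3.7.7), so the 43 patients already enrolled can be handled in the analysis. Late by-visit complaint percentages will look less favourable. The sample size of 76 does not change, and no clinical rule on removal is involved.

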## Discussion

3

This study protocol describes an observational, post-marketing, multicenter case series to collect first evidence on the performance, safety and usability of the J&J MedTech 2.7 mm VA-LCP Clavicle Plate and 2.7 mm Clavicle Hook Plate Systems in a clinical setting. This system is newly developed for the surgical treatment of clavicle fractures and AC joint dislocations—all fixation screws are 2.7 mm in diameter. The system was designed for optimal surface contour fit and implant dimensions, without loss of implant or fixation strength when compared with standard 3.5 mm implants. Since this system has recently been launched on the market, an observational case series with a descriptive analysis is the most appropriate design to collect the first clinical evidence.

One main reason for reoperations after surgical treatment of clavicle fracture and AC joint dislocations is plate prominence (4–7), yet many patients request plate removal for various reasons. In the clinical community, differing opinions exist at both surgeon and country level on plate usage and removal (9, 26). Osteosynthesis with plates may be avoided due to the expected need for a reoperation, conversely plates might be removed as standard to prevent future complications (26). This impacts the overall cost effectiveness of the original surgical treatment using plates, as the cost for plate removal must also be considered (5, 7). Plate removal in asymptomatic cases is different from that for plate prominence, which may be associated with symptoms or complications. Thus, it is important to distinguish between plate prominence and plate removal as reasons for reoperation. Plate prominence is defined as symptomatic excessive subcutaneous prominence of that part of the plate aligned to the shaft or lateral clavicle cortex which may be related to poor fit of the plate to the clavicle, protruding plates or even screw head prominence, the latter of which has been overcome with locking screws or low-profile, non-locking screws (27). Further, plate prominence is influenced by the plate profile and by the fit between the plate and the bone (27). Plate prominence may lead to irritation of the soft tissues and may lead to pain (28), and is the most common reason for reoperation after clavicular shaft plate osteosynthesis (28). Additionally, mismatch of the orientation, angulation or length of the hook region of the clavicular hook plate with respect to the inferior surface of the acromion may cause intrusion into the subacromial space (leading to subacromio-deltoid bursitis and possible extrinsic rotator cuff attritional lesions) or, conversely, erosive attrition of the acromial periosteum and, eventually, bone (leading to bone pain, bone erosion, and possible bone fracture) (29, 30).

With the 2.7 mm VA-LCP Clavicle Plates and 2.7 mm Clavicle Hook Plates used in this study there is a downsizing of the implant/bone interface. As the first all 2.7 mm clavicle plate system it is important to be able to provide data on its clinical safety, but also important data on its clinical performance including complaints related to plate prominence or discomfort and PROs assessing these aspects.

In this study, a prospective, observational design is used which will allow an assessment of the 2.7 mm VA-LCP Clavicle Plates and 2.7 mm Clavicle Hook Plates when they are used per SoC, as the protocol does not influence the clinical decision-making process. MMRM will be used to analyze PROs and QuickDASH, allowing us to consider the within-subject correlations, and adjust for baseline characteristics and other covariates, improving estimate and inference precision. Additional analyses will be adjusted as appropriate, depending on their objectives and model assumptions. The list of confounders and the details of the adjustment methods will be fully specified in the Statistical Analysis Plan. The sensitivity analysis, the analysis restricted to per-protocol population, and the handling of missing data (if deemed necessary) will help assess whether the conclusions remain consistent when accounting for potential biases introduced by major protocol deviations, missing data, and/or patient dropout.

Data gathered from this study can help design comparative studies for relevant performance parameters in the future. Indeed, a limitation of this study is the absence of a control group, yet the results of this study will be useful in future comparative studies, providing a proven treatment arm which could be compared to different treatment options. Also, although this study does not specifically aim to assess cost-effectiveness, the evidence gathered on the need for reoperations may help drive hypotheses development for future studies focused in this area; additionally, a *post hoc* cost-benefit analysis might take place. This study does have some limitations. One limitation of the study protocol is the lack of patient involvement in its development; there may be other outcomes important to patients that are missing from the present study. As a prospective, observational case series without a control or comparator group, this study is limited in its ability to establish causal relationships or directly compare the investigational plates with other fixation methods. The relatively small sample size and potential loss to follow-up may reduce statistical power and generalizability of the findings. Additionally, generalizability to comorbid populations may be limited because the population included is generally healthy with patients with certain comorbidities and polytrauma being excluded. Outcomes rely partly on patient-reported measures, which may be subject to bias, particularly recall, reporting or social desirability biases which may affect how accurately patients describe their symptoms. The multicenter design may introduce variability in surgical technique and postoperative management. This also impacts variability in imaging acquisition as imaging acquisition follows the local standard of care; this limitation of multicenter observational studies will be mitigated using a central reviewer who receives the images in a blinded way and centrally analyses the images at both the interim and final analysis following standardized criteria. Lastly, as the study is multicenter, it is further subject to geographical variability; there may be differences in surgical expertise, health care systems or patient demographics that may influence the results obtained. Nevertheless, the multicenter collaborative effort will provide clinical and safety data from different geographic locations per SoC, providing initial knowledge to form the basis for future clinical research.

## Ethics and dissemination

4

Ethics approval is obtained from the local ethics committee or institutional review board prior to patient enrolment (Corewell Health—West Institutional Review Board CHW-IRB-2025-0954; PRISMA HEALTH IRB 2248577-1; Ethik-Kommission Albert-Ludwigs-Universität Freiburg 24-1346-S1-AV; Ethikkommission Nordwest- un Zentralschweiz 2024-01581; Ethik Kommission Westfalen-Lippe 2024-207-f-S; Wake Forest University Health Sciences IRB IRB00104269; Ethikkommission der Stadt Wien EK 24-096-0824). The registry has been designed and implemented according to current valid international standards (ICH GCP and ISO 14155) and based on the ethical position of the Declaration of Helsinki, to ensure optimal protection of patient interests. For patient enrolment an informed consent process approved by the responsible ethics committee will be followed. It is intended that the results of this study shall be published in peer-reviewed journals. For the publication of the results of this study, all investigators will have access to all data generated and be involved in the decision to publish. This manuscript reflects the current protocol version V1.0 dated September 12, 2023.
